## Abstract

**Background:**

Mental and physical fatigue while at work is common among emergency medical services (EMS) shift workers. Extended shifts (for example 24 hours) and excessive amounts of overtime work increase the likelihood of negative safety outcomes and pose a challenge for EMS fatigue-risk management. Text message-based interventions are a potentially high-impact, low-cost platform for sleep and fatigue assessment and distributing information to workers at risk of negative safety outcomes related to sleep behaviors and fatigue.

**Methods/Design:**

We will conduct a pilot randomized trial with a convenience sample of adult EMS workers recruited from across the United States using a single study website. Participants will be allocated to one of two possible arms for a 90-day study period. The intervention arm will involve text message assessments of sleepiness, fatigue, and difficulty with concentration at the beginning, during, and end of scheduled shifts. Intervention subjects reporting high levels of sleepiness or fatigue will receive one of four randomly selected intervention messages promoting behavior change during shiftwork. Control subjects will receive assessment only text messages. We aim to determine the performance characteristics of a text messaging tool for the delivery of a sleep and fatigue intervention. We seek to determine if a text messaging program with tailored intervention messages is effective at reducing perceived sleepiness and/or fatigue among emergency medicine clinician shift workers. Additional aims include testing whether a theory-based behavioral intervention, delivered by text message, changes ‘alertness behaviors’.

**Discussion:**

The SleepTrackTXT pilot trial could provide evidence of compliance and effectiveness that would support rapid widespread expansion in one of two forms: 1) a stand-alone program in the form of a tailored/individualized sleep monitoring and fatigue reduction support service for EMS workers; or 2) an add-on to a multi-component fatigue risk management program led and maintained by employers or by safety and risk management services.

**Trial Registration:**

Clinicaltrials.gov NCT02063737, Registered on 10 January 2014

## Background

Fatigue is ‘a subjective, unpleasant symptom, which incorporates total body feelings ranging from tiredness to exhaustion creating an unrelenting overall condition which interferes with individual’s ability to function to their normal capacity’ [1]. Fatigue can be linked to inadequate or disturbed sleep and is a common problem among workers in industries that provide 24-hour/day services, including healthcare [2]. There is compelling evidence linking sleep, fatigue, and shiftwork to negative safety outcomes [3]. One study determined that fatigue at the time of a workplace injury was eight times more likely among healthcare workers that worked shifts longer than 12 hours in duration [4]. Scheduled naps, exercise, modifying sleep habits, and use of caffeine ameliorate the effects of poor sleep, fatigue, and decreased alertness [5-13].

Unfortunately, many shift workers may not adopt such solutions and commonly sacrifice sleep health for economic reasons, family work-life reasons, or other factors [2,14]. For these workers, solutions need to be tailored to their shiftwork lifestyle, have an impact, and be timely. For employers of these workers, solutions should be economically viable, modifiable to changes in shift structure, and scalable for an entire workforce.

Emergency medical services (EMS) clinicians are a group of workers where extended shifts, inconsistent shift patterns, poor sleep, and fatigue are common [14-17]. There are an estimated 19,000 EMS organizations and 800,000 to 1 million licensed EMS workers in the United States today [18]. EMS workers are often the first point of clinical contact for the acutely ill and injured. Many EMS workers work for extended periods (for example 24 hours), often consecutively, and may accumulate many hours of overtime [14-17]. Half of EMS workers sleep less than six hours per sleep period and many report poor sleep quality [16]. One-third of EMS workers report excessive daytime sleepiness [19]. High workload combined with limited or poor sleep contributes to half of all EMS workers reporting excessive mental and physical fatigue while at work [15,16].

Survey data show convincing relationships between sleep, fatigue, and safety outcomes in EMS workers [16]. The odds of injury are 1.9 times greater among fatigued EMS workers than the non-fatigued; after controlling for confounding [16]. The odds of making an error or experiencing a patient-related adverse event are 2.2 times greater among fatigued EMS workers than the non-fatigued [16]. Fatigue and poor sleep increase the likelihood of risky behaviors. The odds of engaging in behaviors that compromise patient or worker safety (such as driving at high speeds in an ambulance when potentially not necessary) are 3.6 times greater among EMS workers that report fatigue [16]. Unfortunately, shift structure in EMS, a potential contributor to fatigued EMS workers, is not widely regulated and there is little to no incentive to recognize or admit to fatigue while on the job. Few EMS agencies have an evidence-based fatigue risk management program, and there is limited evidence of any best practices for lessening fatigue in the EMS industry.

As in other shift work populations, popular strategies to address poor sleep and fatigue among shift workers include scheduled naps, shift length modification, caffeine, and mental and physical exercise [5-13,20]. However, the effectiveness of any one or combination of these strategies in an EMS organization has not been widely studied. Boudreaux *et al.* evaluated the impact of eliminating 24 hour shifts in favor of 12 hour standard shifts in one medium-sized EMS agency [20]. Short-term impacts included lower perceived burnout and a more positive perception of work-life balance [20]. These findings returned to pre-intervention levels after 12 months [20]. One study of 10 EMS workers in Japan showed that scheduled naps while on duty had no impact on reaction time or self-reported fatigue compared to workers without naps [21]. Wide variation in EMS worker shift schedules, sleep habits and behaviors, and knowledge of sleep hygiene and signs/symptoms of fatigue are obstacles for any intervention and may have impacted the findings of previous research. Other obstacles include employers preoccupied with day-to-day challenges that do not involve worker sleep or fatigue. Some organizations may unintentionally encourage extended shifts in order to maintain full staffing and reduce operating costs without knowledge of the impact on worker sleep, fatigue, and safety. Poor workplace safety culture is prevalent in many EMS organizations and may further impact the likelihood that employers invest in worker sleep hygiene and fatigue-reduction programs [22,23]. The complex nature of sleep and fatigue in EMS shift workers, combined with economic and systems-level operation pressures such as maintaining 24 hour readiness, demands that innovative solutions and strategies be tested and developed in an EMS setting.

There is growing enthusiasm and preliminary data to support the use of mobile technologies and real-time interventions using cell phones or smartphones [24,25]. More than 90% of Americans own a cell phone and 55% own a smartphone [26,27]. More than 80% of cell phone owners send or receive text messages, 60% access the internet on their phone, and 52% send or receive email via their cell phone or smartphone [26]. A 2012 systematic review of mobile health (mHealth) intervention studies identified a positive impact on select behaviors using text messaging of intervention materials and messages (smoking, diabetes control, weight loss, and asthma self-management) [25]. Other reviews identify many studies with positive findings, yet temper support for mHealth-based interventions without additional high quality randomized controlled trials [24].

Tailored mHealth interventions may benefit EMS worker sleep habits and behaviors related to fatigue. For example, adherence to a well-organized behavioral change program for sleep has been shown to reduce the signs and symptoms of insomnia and improve self-reported sleep health [28]. A common challenge with any behavioral intervention has been longterm adherence and maintenance [29,30]. Adherence may be impacted by an acute change in lifestyle (such as shiftwork patterning) or a change in motivation related to the loss of continued support, coaching, or ongoing engagement [29-31]. Prior studies show ongoing support and engagement via telephone or web-based contact can improve adherence to an intervention; yet results from strictly web-based interventions are generally less positive [32]. Preliminary results from behavioral change studies using text messaging show positive sustained adherence of behavioral change [33]. Text message-based interventions are a potentially high-impact, low-cost platform for promoting positive sleep habits, tracking sleepiness and fatigue, and distributing information to EMS shift workers at risk of negative safety outcomes related to sleep behaviors and fatigue.

In this paper, we present the study protocol for a controlled 90-day pilot trial with an assessment-only control group. This study has two objectives. First, we aim to determine the performance characteristics of a text messaging tool as the prime vehicle for delivery of a sleep and fatigue intervention for EMS shift workers. Second, we aim to determine if a short message service (SMS) program with tailored intervention messages is effective at reducing perceived sleepiness and/or fatigue among emergency medicine clinician shift workers. Additional aims include testing whether a theory-based behavioral intervention, delivered by SMS, changes any one of eight factors that are hypothesized to impact ‘alertness behaviors’. These factors are based on the Integrative Model of Behavioral Prediction and include: 1) attitudes, 2) perceived norms, 3) self-efficacy, 4) knowledge, 5) salience, 6) habits, 7) environmental constraints, and 8) behavioral intent. We hypothesize that performance (study subject compliance) with text message assessments will be high and that our SMS behavioral intervention distributed via text messaging will show a reduction in perceived fatigue at the end of shiftwork. We hypothesize that our intervention will impact one or more of the eight factors predictive of alertness behaviors. Study findings will provide important preliminary data to address key questions related to the feasibility and performance of an SMS platform to address sleep and fatigue among shift workers.

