## Methods/Design

### Trial design

The SleepTrackTXT study is a single center, two-arm, parallel, single blind, randomized controlled trial. We use a study webpage as our main means of recruitment. Eligible participants contact the study team to request enrollment and undergo screening. We will randomize 100 emergency workers to one of two groups (N = 50 each). The intervention group will receive 90 days of automated SMS (text messaging) dialogue via a computer. Messages to the subjects will include questions on perceived sleepiness, fatigue, difficulty with concentration, work-related injury at the start, during, and end of scheduled shifts. If subjects in the intervention arm report a high level of sleepiness or fatigue at the beginning of or during their shift the computer recommends one of four evidence-based strategies for improving alertness and reducing sleepiness or fatigue during their shiftwork. The control group subjects will participate in a 90-day SMS dialogue with the computer. In this group, the computer will ask at the start, during, and end of shifts about sleepiness, fatigue, difficulty with concentration, and work-related injury, but the computer will make no recommendations to improve alertness and reduce sleepiness or fatigue. The details of this study design are described below in accordance with the CONSORT statement. Figure 1 provides a visual illustration and flow chart of the SleepTrackTXT trial. This study was approved by the University of Pittsburgh Institutional Review Board and is registered at clinicaltrials.gov (registration number: NCT02063737). All subjects are required to give informed consent.

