#### Sample size

In planning the study, several unknowns prevented a well-informed sample size analysis including the number of shifts each participant would contribute and the amount of correlation in fatigue between multiple shifts within the same subject. We assumed that compliance would be high for all study subjects, with over 80% of text message assessments answered [42]. Due to the pilot nature of the study, we conservatively assumed a minimum of one observation per person and then determined the number we would need to see a large effect size for the ‘proof-of-concept’ outcome. Based on our previous cross-sectional data [15,16] we assumed that 50% of EMS workers would report fatigue at the beginning of or during shift (at risk population). If N = 25 per study arm, we will have 80% power to detect a large effect size of 0.78 difference in the mean end of shift fatigue score between control and intervention groups (alpha = 0.05), using a two-sample Mann-Whitney U test power analysis (PASS software, NCSS Statistical Software, Kaysville, Utah, United States) assuming the actual distribution is logistic. Given the 50% expected rate of fatigue at baseline, we will recruit and randomize 100 participants (50 per group) to obtain the ‘at risk’ number needed within each arm.

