#### Statistical analysis

We will describe overall number of shifts per provider and the mobile text participation for all study subjects. For example, we will quantify compliance with our text message queries and the number that were lost to attrition. We will use linear mixed-model analyses to examine the effectiveness of the intervention on reducing reported fatigue at the end of shift among all participants and among only those reporting fatigue at baseline. We will construct a model where the outcome is the reported fatigue at the end of each shift, a fixed effect for experimental group, a fixed effect of time in study, and a random effect for subjects to account for multiple shifts within each person. We will examine the estimated change in fatigue score per shift in the intervention group compared to the control group. Post-estimation testing will be used to describe the correlation in fatigue scores within the subjects across shifts. The same methodology will be used to analyze end of shift sleepiness and difficulty in concentrating.

The eight scale components of the SFAB survey are measured at baseline and at the end of the study. Likert responses will be scored as continuous measures and weighted from 0 to 100, with higher scores indicating more positive scores. We will test for changes over time and between-group differences in these scales using one sample and two sample t-tests, assuming the underlying distribution of the outcomes are normal. If the data are highly skewed we will use non-parametric tests including the sign rank test and Mann-Whitney U test. All statistical testing will be two-sided with alpha set at <0.05 using STATA version 10 SE (StataCorp LLP, College Station, Texas, United States) and SAS version 9.2 (SAS Institute Inc., Cary, North Carolina, United States).

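### The hypothesis that one or more of eight SFAB factors is affected is tested with each scale at 0.05 and no stated adjustment, so its false-positive rate is well above 5%

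*Protocol article*

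**What the plan says.** In the Background, after the two main objectives, the protocol article adds the aim of testing whether the text-message intervention "changes any one of eight factors that are hypothesized to impact" alertness behaviours. The matching hypothesis is: "We hypothesize that our intervention will impact one or more of the eight factors predictive of alertness behaviors".

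The Statistical analysis section says how this will be examined. "The eight scale components of the SFAB survey are measured at baseline and at the end of the study". Then: "We will test for changes over time and between-group differences in these scales using one sample and two sample t-tests", with signed-rank and Mann-Whitney tests as fallbacks for skewed data. The level is fixed for everything: "All statistical testing will be two-sided with alpha set at <0.05". The article names no primary SFAB scale, global test, testing order or adjustment across the eight.

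The primary intervention outcome is end-of-shift fatigue (Shift level measures and primary outcome), not the SFAB.

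**The concern.** The hypothesis is a disjunction: read literally, an effect on any one of the eight factors makes it true. The natural way to judge it with eight separate tests is to look for at least one significant scale. If each scale is tested at 0.05, the chance of finding at least one by luck is larger than 0.05, and how much larger depends on how strongly the scales are correlated.

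At stake is the behavioural claim. The Discussion presents the study of behaviour and behavioural intent as a strength of the design, and proposes to use the SFAB data to identify subgroups that benefit most or need a special intervention. A chance finding on one scale could be reported as support for the theory behind the messages.

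**Working it through.** **The plan's own figure.** The article states no error rate for the SFAB scales. Its only power statement concerns fatigue: "If N = 25 per study arm, we will have 80% power to detect a large effect size of 0.78 difference", by a Mann-Whitney test, "assuming the actual distribution is logistic". The efficiency of that test relative to the t-test for logistic data is π²/9 = 1.097, so the effective size is 25 × 1.097 = 27.4 per arm. A two-sided t-test at 0.05 with effect size 0.78 then has 80.9% power, and simulating the Mann-Whitney test on logistic data (20,000 runs) gives 79.1%. The stated 80% reproduces. It has no bearing on the SFAB tests.

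**Inputs for the SFAB check.**
- Eight scales, each compared between arms (Statistical analysis).
- Two-sided 0.05 per test (Statistical analysis).
- 50 per arm: "We will randomize 100 emergency workers to one of two groups (N = 50 each") (Trial design).
- Common correlation ρ between the scales: not in the article, so an assumption, varied from 0 to 0.9.

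**Independent scales, either direction.** 1 − (1 − 0.05)^8 = 1 − 0.95^8 = 0.337.

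**Correlated scales, either direction.** With φ and Φ the standard normal density and distribution function and c = 1.96, the chance of at least one significant scale is

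1 − ∫ φ(u) [Φ((c − √ρ·u)/√(1−ρ)) − Φ((−c − √ρ·u)/√(1−ρ))]^8 du.

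**Favourable differences only.** Each test has 0.025 in the favourable tail. For independent scales this gives 1 − 0.975^8 = 0.183. For correlated scales the bracket above reduces to its first term.

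| Assumed ρ | Either direction | Favourable only |
|---|---|---|
| 0 | 33.7% | 18.3% |
| 0.3 | 30.0% | 15.2% |
| 0.5 | 25.0% | 12.5% |
| 0.7 | 19.1% | 9.5% |
| 0.9 | 11.9% | 6.0% |

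The reference values for a single test are 5% (either direction) and 2.5% (favourable only).

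**Check by simulation.** Eight two-sample t-tests with 50 per arm and no effect gave at least one significant result in 33.5% (ρ = 0), 25.0% (ρ = 0.5) and 19.3% (ρ = 0.7) of 20,000 runs, in agreement with the integral.

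**After adjustment.** When no scale is affected, Holm rejects something only if the smallest p-value is below 0.05/8 = 0.00625. The chance of that is 1 − (1 − 0.00625)^8 = 4.9% at ρ = 0 and 3.1% at ρ = 0.7.

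**Power cost.** With 50 per arm, complete data and a two-sided t-test, the standardized difference detectable with 80% power is 0.57 at 0.05 and 0.73 at 0.00625.

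**The case against.** The strongest reply is that this concerns an additional aim of a pilot that promises preliminary data, measured with a survey the investigators developed themselves and that still consists of candidate items. Statisticians differ on whether family-wise error needs control across exploratory scales, and multiplicity rules for such outcomes are often left to an analysis plan, which is not shown here. The sentence on alpha is also generic: an adjusted p-value can be judged against 0.05 too. And the article nowhere says that one p-value below 0.05 confirms the hypothesis.

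Much of this stands, and it limits the weight of the point. It does not remove it. The article does more than stay silent: it states a disjunctive hypothesis and a single level for all tests, and a reader who follows both obtains the error rates above. A claim of at least one effect among several is the case where adjustment is needed. That one significant scale suffices remains a reading, adopted because the article offers no other criterion.

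Three stronger readings are tempting, and the article does not support them.
- A reader might infer that a useless intervention would appear to work in 19–34% of trials. That range counts differences in both directions, which suits the neutral wording of the aim and hypothesis. The scales have a favourable direction, however, and in that direction the corresponding figures are 9.5–18.3%. The lower end of each range also rests on an assumed correlation of 0.7.
- A reader might add the one-sample tests of change and arrive at error rates of 30–50%. That requires change within the intervention arm alone to count as an effect of the intervention. The article does not say so.
- A reader might suppose that behavioural intent is the natural single factor to test. Nothing in the article ranks it above the other seven for testing.

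**Conclusion.** The point holds in a limited form. If one significant between-arm scale is taken as support for the hypothesis, its false-positive rate is 33.7% for independent scales and still about 12% at a common correlation of 0.9, against a nominal 5%. For favourable differences only it runs from about 18% (correlation 0) to 9.5% (0.7) and 6% (0.9), against 2.5% for one test. These figures assume no effect on any scale and equal correlation between all pairs of scales; the correlation itself is unknown. They count the eight between-arm tests only.

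The severity is moderate. The fatigue outcome, the compliance outcome and the sample size do not depend on these tests.

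**What to change.** Add one sentence to the Statistical analysis section: the conclusion that one or more factors were affected will rest on the eight between-arm SFAB comparisons, with Holm adjustment and an adjusted p-value below 0.05. Report the unadjusted scale-level results and the one-sample tests of change as exploratory estimates with confidence intervals.

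No data collection changes. Trial status says follow-up data were still being collected when the article was accepted; the rule should be fixed before the SFAB data are analysed. The cost is power per scale: at the strictest Holm step the detectable standardized difference rises from 0.57 to 0.73, and a true difference of 0.57 on one scale, which has 80% power at 0.05, has about 52% at 0.00625. Missing 90-day surveys would lower power further.

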## Methods/Design

### Trial design

The SleepTrackTXT study is a single center, two-arm, parallel, single blind, randomized controlled trial. We use a study webpage as our main means of recruitment. Eligible participants contact the study team to request enrollment and undergo screening. We will randomize 100 emergency workers to one of two groups (N = 50 each). The intervention group will receive 90 days of automated SMS (text messaging) dialogue via a computer. Messages to the subjects will include questions on perceived sleepiness, fatigue, difficulty with concentration, work-related injury at the start, during, and end of scheduled shifts. If subjects in the intervention arm report a high level of sleepiness or fatigue at the beginning of or during their shift the computer recommends one of four evidence-based strategies for improving alertness and reducing sleepiness or fatigue during their shiftwork. The control group subjects will participate in a 90-day SMS dialogue with the computer. In this group, the computer will ask at the start, during, and end of shifts about sleepiness, fatigue, difficulty with concentration, and work-related injury, but the computer will make no recommendations to improve alertness and reduce sleepiness or fatigue. The details of this study design are described below in accordance with the CONSORT statement. Figure 1 provides a visual illustration and flow chart of the SleepTrackTXT trial. This study was approved by the University of Pittsburgh Institutional Review Board and is registered at clinicaltrials.gov (registration number: NCT02063737). All subjects are required to give informed consent.

